## Abstract

**Background:**

Many people with dementia experience anxiety, which can lead to decreased independence, relationship difficulties and increased admittance to care homes. Anxiety is often treated with antipsychotic medication, which has limited efficacy and serious side effects. Cognitive behavioural therapy (CBT) is widely used to treat anxiety in a range of populations, yet no RCTs on CBT for anxiety in dementia exist. This study aims to develop a CBT for anxiety in dementia manual and to determine its feasibility in a pilot RCT.

**Methods/design:**

Phase I involves the development of a CBT for anxiety in dementia manual, through a process of (1) focus groups, (2) comprehensive literature reviews, (3) expert consultation, (4) a consensus conference and (5) field testing. Phase II involves the evaluation of the manual with 50 participants with mild to moderate dementia and anxiety (and their carers) in a pilot, two-armed RCT. Participants will receive either ten sessions of CBT or treatment as usual. Primary outcome measures are anxiety and costs. Secondary outcome measures are participant quality of life, behavioural disturbance, cognition, depression, mood and perceived relationship with the carer, and carer mood and perceived relationship with the person with dementia. Measures will be administered at baseline, 15 weeks and 6 months. Approximately 12 qualitative interviews will be used to gather service-users' perspectives on the intervention.

**Discussion:**

This study aims to determine the feasibility of CBT for people with anxiety and dementia and provide data on the effect size of the intervention in order to conduct a power analysis for a definitive RCT. The manual will be revised according to qualitative and quantitative findings. Its publication will enable its availability throughout the NHS and beyond.

**Trial registration:**

ISRCTN64806852

## Background

In the UK, over 700,000 older people have dementia, placing an enormous strain on public services and family carers [1]. There are limits in the effectiveness and use of dementia medication [2] and in recent years there has been an increase in the development of psychosocial treatments for dementia [3]. Anxiety is common in dementia, with prevalence estimated from 5-21% for anxiety disorders and up to 71% for anxiety symptoms [4]. In addition to excessive worries and fears, anxiety may physically manifest as agitation, motor restlessness, day/night disturbance and aggression. It has been associated with high physical dependency and problems in the patient/carer relationship [5], decreased independence and limitations in activities of daily living [6], increased behavioural problems [7] and increased admissions to nursing care [8]. Anxiety is often treated with antipsychotic medication, which has limited efficacy and serious side effects, including sedation, depression, stroke and cognitive deterioration [9].

Cognitive behaviour therapy (CBT) [10] focuses on the interplay among people’s thoughts, feelings and behaviour. It primarily focuses on the here and now, is highly collaborative and aims to identify personalised, time-limited goals and strategies that are put into practice between sessions (“homework”). There is robust evidence that CBT is an effective first-line strategy for anxiety in general adult populations [2] and for cognitively intact older people [11]. CBT has been widely adopted by the NHS, for example ‘Improving Access to Psychological Therapies’ (IAPT) [12] aims to support primary care trusts in implementing CBT for depression and anxiety in people of 'working age'.

People with dementia have diminished cognitive resources, but there is evidence that they can learn and develop skills, even when moderately cognitively impaired [13]. This suggests that CBT in an adapted form could be used with this client group, as it has been in other impaired populations such as those with learning disabilities [14]. There is evidence for the effectiveness of CBT for depression in dementia, primarily through case studies and an RCT by Teri et al. [7]. There are only four small studies examining CBT for anxiety in dementia. Kipling et al. [15] found changes in behaviour, cognition and mood in a group of three people. Koder [16] and Kraus et al. [17] each described two individual cases and found clinically meaningful reductions in anxiety, plus improved mood and participation in pleasurable activities [17], and reduction in alcohol intake and night awakenings [16]. Paukert et al. [18] developed Peaceful Mind, a CBT intervention for anxiety and dementia, finding reductions in anxiety, depression and carer distress in an open trial containing eight individuals. All four studies suggest that CBT in people with dementia is feasible and concluded that larger trials are now needed, yet there are no published RCTs in CBT for anxiety for dementia.

There will be two phases to this trial, which correspond to phase I and II of the MRC’s guidelines for developing a complex intervention and assessing feasibility [19]. The key aims are:

(1) To develop a CBT intervention manual.

(2) To assess the feasibility of the intervention through a single-blind, pilot RCT on CBT versus treatment as usual (TAU) for people with dementia and their carers. This will include an assessment of acceptability, compliance, recruitment and retention.

(3) To conduct qualitative interviews with participants, assessing the acceptability of the treatment and examining whether changes generalised.

## Method

### Phase I: Development phase

This phase consisted of four stages:

1. *Focus groups:* We conducted nine focus groups with service-users (people with dementia, family carers and staff groups) on causes and management of anxiety [20]. Emerging themes included coming to terms with the diagnosis and loss of skills as causes, and person-centred care, memory aids and medication as a last resort in terms of management.

2. *Comprehensive literature reviews:* We have published the protocol for a Cochrane systematic review on psychosocial interventions for anxiety and depression in dementia [21] and are currently writing the full review. The findings of relevant studies identified in the Cochrane review along with the focus group findings and outcomes of a comprehensive review of the literature on CBT for anxiety (in general populations and with older adults) were used to adapt the best features and identify key techniques and potential adaptations and generate version 1 of the manual.

3. *Expert consultation*: Version 1 of the manual was sent to three experts in dementia and/or CBT and revised according to their comments, generating version 2.

4. *Consensus process:* A Delphi process [22] is commonly used to reach consensus when defining new interventions in health service research. We used a modified Delphi process, outlining a set number of cycles at the outset. Version 2 was brought to an advisory panel of 30 multidisciplinary experts (psychologists, psychiatrists, CBT therapists, carers, admiral nurses and occupational therapists) at a half-day consensus conference. Different parts of the manual were discussed by small groups, with the aim of generating feedback and suggestions for modifications. Amendments following the consensus conference generated version 3 of the manual.

5. *Field testing:* Version 3 was field tested with three people with dementia and their carers, which generated information about modifications needed to improve its feasibility and relevance in practice. These data were used to develop version 4 of the manual, which was sent back to an expert panel for further comments. Further modifications resulted in version 5, to be used for the trial.

### Phase 11: Intervention phase

#### Design

The design is a single-blind, multicentre, pilot RCT of CBT plus treatment as usual (TAU) versus TAU for people with dementia. Patient-carer dyads will be randomly allocated to either CBT or TAU. As no trials have been done in this area, we were unable to estimate the likely effect size of this intervention. We will recruit 50 participants with power set at 80%, *p* = 0.05. This will be adequate to detect an effect size of 0.8 or above. An objective of this study is to provide data on the actual effect size of the intervention in order to do a power analysis for a definitive RCT. Figure 1 shows the trial design.

**Figure 1 F1:**
[figure not shown]
CBT for anxiety in people with dementia flow diagram.

#### Participants

Fifty participants and their carers will be recruited through North East London Foundation Trust (NELFT) and North Essex Partnership NHS Foundation Trust (NEPFT). Recruitment will be through memory services, community mental health teams, admiral nursing teams and outpatient referrals.

Inclusion criteria are:

1. Meet DSM-IV criteria for dementia in mild to moderate range, Clinical Dementia Rating (CDR) [23] score of 0.5, 1 or 2.

2. Clinical anxiety, as determined by a score of 11 or above on the Rating Anxiety in Dementia scale (RAID) [24].

3. Living in the community.

4. The presence of a carer who is willing to participate in the therapy.

5. An ability to understand and communicate in English.

6. Willing to engage in therapy involving discussion of thoughts and feelings.

Exclusion criteria are:

1. Co-morbid psychiatric disorder (e.g. psychosis) or challenging behaviour (e.g. severe agitation) likely to prevent engagement in therapy.

2. Presence of a learning disability or severe physical illness that could impact on participation.

#### Ethical considerations

Ethical approval was obtained through the East London 3 Research Ethics Committee (ref. no. 10/H0701/124). Informed consent will be sought from participants and their carers, using current guidance from the British Psychological Society on evaluation of capacity. Participants may withdraw from the trial at any time without giving a reason. The withdrawal of the participant from the trial will not affect their access to other appropriate treatments or services.

All information disclosed in the study will be kept confidential, and participants will not be identifiable in any material published as part of the study in any way. All data are stored without any identifying details under secure conditions and all tapes will be destroyed at the end of the trial. In line with Standard Operating Procedures for the study, the reporting of Serious Adverse Events will be made to the Chief Investigator. The Chief Investigator will then inform the Research & Development Manager and Trust Governance Manager. Local policy and procedures will be followed for reporting and investigating serious untoward incidents.

#### Randomisation

Randomisation will be conducted by telephoning an independent administrator within PRIMENT Clinical Trials Unit after the participant/carer has provided informed consent and baseline data. The randomisation schedule is being developed by an independent statistician in PRIMENT, and blocking will be employed (with block sizes varying between 4 and 6) to help ensure equal numbers in the intervention and control arms.

#### Interventions

CBT plus TAU: The patient-carer dyads will participate in 10 weekly sessions, each lasting 1 h hour. This number was determined on the basis of the published literature, the team’s experience and patient and carer feedback.

The manual is divided into four phases. Phase 1 involves assessment and formulation. Key aims are to build a collaborative relationship, socialisation to the CBT model, identifying goals and establishing the involvement of the carer. The carer’s role is to support the person with dementia in implementing strategies, for example applying what has been discussed during sessions in everyday life. Their involvement could range from very little (e.g. attending brief parts of some sessions) to being present at all times. Phase 2 involves the application of change processes, which the therapist will adapt according to the needs and strengths of the individual. These include identifying and practicing strategies for feeling safe, identifying and challenging unhelpful cognitions, ‘realistic negative automatic thoughts’, calming thoughts (on cue cards) and behavioural experiments. Phase 3 works on ending the therapy and developing a blueprint for the future. This includes reviewing and consolidating learned skills, integration of skills into everyday life and considering the future involvement of carers and others.

Sessions will cover themes and broad ideas, but there will be specific guidelines on how to adapt them to suit the needs of individuals. For example, the degree to which ‘cognitive’ and ‘behavioural’ elements are used will vary, with higher functioning participants being more able to access the ‘cognitive’ and a greater emphasis on behavioural aspects with the more impaired.

For some, sessions may need to be shortened or breaks may be required to maximise attention.

Telephone contact will be offered between sessions to answer questions and encourage ongoing work, should it be required. Sessions will be delivered by clinical or counselling psychologists, with experience of working with people with dementia. They will be given regular clinical supervision by a senior old age clinical psychologist with specialist CBT training.

Treatment as usual (TAU): This is defined as the standard treatment available to people with anxiety and dementia, which is most likely to include medication or no treatment.

#### Outcome measures

All outcome measures will be administered by the main research assistant, blind to group allocation, at week 1 (baseline), week 15 (follow-up 1) and 6 months (follow-up 2). Fifteen weeks for follow-up 1 was determined by the field-testing phase, which suggested that it takes an average of 15 weeks to complete a ten-session intervention because of factors such as randomisation time, illness and holiday. Demographics and general information will be collected including age, gender, ethnic group, use of medication (including anxiolytics and cholinesterase inhibitors), treatment preference and participation in other activities. The Clinical Dementia Rating (CDR) [23] will be used to provide a global rating of dementia severity as part of the general background information.

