#### Primary outcome measures

1. **Rating Anxiety in Dementia** (RAID) [24]. This rates signs and symptoms of anxiety using interviews with carers and people with dementia. There are 18 questions in four categories: worry, apprehension, vigilance, motor tension and autonomic hypersensitivity. A score of 11 or above indicates significant clinical anxiety. It has good inter-rater and test-retest reliability, is sensitive to change and correlates with quality of life [25].

2. **Clinical Services Receipt Inventory** (CSRI) [26]. A tool that collects information about the interviewee’s use of health and social care services, accommodation and living situations, income, employment and benefits, and any changes that may be incurred in the receipt of these services (after the therapy).

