#### Qualitative interviews

After follow-up 1, 12 patient-carer dyads who received CBT will be invited to take part in qualitative interviews, led by another research assistant (to ensure blindness to treatment) and lasting approximately 1 hour. Issues addressed will include experiences of the sessions, views on themes and techniques, and benefits/changes identified in everyday life. Interviews will be audio recorded and transcribed. Framework analysis [33] will be used to extract themes and draw conclusions.

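### The blinded assistant who rates anxiety also administers the service-use inventory, which is likely to reveal CBT allocation: a threat at 6 months in any order, and at week 15 if the inventory comes first

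*Protocol article*

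**What the plan says.** The Outcome measures section assigns everything to one person: "All outcome measures will be administered by the main research assistant, blind to group allocation". It makes no exception for any instrument. The visits it names are "at week 1 (baseline), week 15 (follow-up 1) and 6 months (follow-up 2".

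The Primary outcome measures section lists two instruments under that rule. For RAID it says: "This rates signs and symptoms of anxiety using interviews with carers and people with dementia". The second is the CSRI, whose content includes "use of health and social care services, accommodation and living situations, income, employment and benefits". The description then extends this to "any changes that may be incurred in the receipt of these services (after the therapy".

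Under Interventions, for the CBT arm: "The patient-carer dyads will participate in 10 weekly sessions", delivered by clinical or counselling psychologists. The comparator is standard treatment, "which is most likely to include medication or no treatment".

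The Qualitative interviews section handles a similar risk differently. Those interviews, held after follow-up 1 with dyads who received CBT, are "led by another research assistant (to ensure blindness to treatment".

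**The concern.** The person who must not know the allocation is given an instrument that asks about the kind of contact that separates the arms. A run of weekly psychologist appointments is a health service contact, and in this trial it points strongly to CBT.

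Patients and carers know what they received, so the single-blind description rests on the assessor. The assessor's judgement enters the anxiety score. If that assessor learns the arm, expectation can move the RAID difference. The Statistical analysis section uses the confidence interval around the anxiety effect size to help set the sample size of the full-scale trial, so a shift here would carry into the next design.

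The protocol already accepts that talking about therapy can unblind an assessor, because it uses separate staff for the qualitative interviews. It does not extend that separation to the CSRI.

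**Working it through.** The point is procedural, so the main check is to read the sections together, visit by visit.

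**Inputs**
- One blinded assistant gives all measures (Outcome measures).
- The CSRI is one of those measures and asks about services used (Primary outcome measures).
- Ten psychologist sessions are scheduled in the CBT arm only (Interventions).
- RAID and Cornell are described as rated from interviews (Primary and Secondary outcome measures). The article does not say how the NPI is completed; it is treated here as interviewer-rated too.
- Randomisation follows consent and baseline data (Randomisation).
- Week 15 was chosen because a ten-session course took that long on average in field testing (Outcome measures).

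**Visit by visit**
1. *Baseline.* Not affected. The dyad has not been randomised, so there is nothing to disclose.
2. *Week 15.* Therapy has typically just finished, so the sessions are recent. If the CSRI is given before RAID, Cornell or NPI, a CBT dyad that mentions its sessions unblinds those ratings. If the ratings are completed first, the CSRI cannot unblind them. The article states no order.
3. *6 months.* The same assistant returns, having heard the week-15 CSRI answers. Whatever the order at this visit, the assistant may already know the arm.

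**Number at risk**
The plan's own figure of 50 reproduces. For a standardised effect of 0.8, two-sided 5% and 80% power, n per arm = 2 × (1.96 + 0.84)² / 0.8² = 2 × 7.84 / 0.64 = 24.5, rounded up to 25, so 50 in total. That figure is not in dispute. With blocking for equal arms, 50 / 2 = 25 dyads are in the CBT arm. This is the number at risk of disclosing, not a count of dyads who will.

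**What a bias would do**
Suppose knowledge of the arm shifts the mean RAID difference by b standard deviations. The estimated effect becomes d + b, and both confidence limits move by about b. Sample size varies as 1/d², so a full-scale trial planned on d + b would have (d / (d + b))² of the size needed for the true effect d. With b in favour of CBT, that trial would be too small. The documents give no value for b, so no number is put in.

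**The case against.** Four points deserve a fair hearing.

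**Disclosure is an inference.** The CSRI form is not shown, and the article does not say whether trial sessions are recorded on it. The plan has other sources of session data: an adherence checklist, audio recording of all sessions, and number of sessions received as a predictor in the analysis. The reference to the therapy in the CSRI description may mark only the time at which changes in services are measured. This stands. A reader might infer that every CBT dyad will be unmasked and the blind broken systematically. The documents do not support that; they support likely disclosure.

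**The article is condensed.** Instrument order, instructions to dyads and checks on blinding are commonly left to a fuller document, and their absence is not the point here. What remains is a conflict in what is stated: all measures, one blinded assistant, and a service-use interview among them. The article states the separation of staff for the qualitative interviews and states none for the CSRI.

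**Week 15 may be intact.** A reader might infer that all follow-up ratings are compromised. That does not follow. If RAID is rated first, the week-15 rating can still be blind.

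**Size and consequence.** A reader might attach a figure to the bias, for instance as a share of the 0.8 design effect. Nothing in the documents supports one, and 0.8 is only the effect the trial could detect; the Design section says the likely effect could not be estimated. The analyses are exploratory and feasibility is the main aim, so no definitive efficacy claim rests on RAID. This limits the harm but does not remove it, because the anxiety effect size is a stated product of the pilot.

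**Conclusion.** The concern holds as a likely threat to assessor blinding that arises from following the plan as written. It applies to RAID, Cornell and NPI at week 15 only if the CSRI is given first, and at 6 months in any order. About 25 CBT dyads are at risk of disclosing. How many would do so, and by how much ratings would shift, is unknown.

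The conclusion rests on three assumptions: that the CSRI as used does not already exclude trial sessions, that the same assistant carries out both follow-ups as stated, and that weekly psychologist contact is uncommon under treatment as usual, as its description suggests. If the first is false, the risk falls to spontaneous disclosure, which no assignment of instruments can fully prevent.

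This is worth correcting because the remedy is modest and protects the estimate intended to inform the full-scale trial. It does not undermine the feasibility aims.

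**What to change.** Amend the Outcome measures section in two steps.

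1. **Order, at both follow-ups.** The blinded assistant completes RAID, Cornell and NPI before any service-use question. Alone, this protects only the week-15 ratings.
2. **To protect the 6-month ratings, one of two routes:**
   - The research assistant already used for the qualitative interviews collects the CSRI, for example by telephone.
   - The CSRI is worded to exclude trial sessions, these are counted from therapy records, and dyads are asked not to mention them to the assessor. This needs no extra contact but relies on participants, some with moderate dementia, keeping to the request.

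**Cost.** Reassignment adds one short contact per dyad per follow-up: 50 × 2 = up to about 100 if applied to everyone. The article does not say that the second assistant is available through the 6-month visits, so this should be confirmed first. Either route changes procedure partway through: 25 of 50 participants were already recruited, and any dyad past its week-15 CSRI may already have disclosed. The date of the change and the dyads assessed under each procedure should be documented. Sample size and analysis need not change.
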